**Methods:**

This protocol describes a factorial, randomized, controlled pilot study that employs a 2 (affective imagery: positive, neutral) by 2 (EFT: yes, no) design in which participants are randomized to 1 of 4 guided imagery intervention arms. In total, 156 eligible participants will complete 2 lab visits separated by 5 days. At visit 1, participants complete surveys; listen to the audio guided imagery intervention; and complete TD, food demand, and food choice tasks. At visit 2, participants complete TD, food demand, and food choice tasks and surveys. Participants complete a daily food frequency questionnaire between visits 1 and 2. Analyses will compare primary outcome measures at baseline, postintervention, and at follow-up across treatment arms.

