### Experimental Sessions

The study protocol includes 2 in-lab experimental sessions separated by approximately 5 days of at-home daily food diary entries (see Table 1). All questionnaires, intervention content, and baseline and outcome measures are delivered via the Qualtrics Web-based survey platform. Participants will be asked to fast for 2 hours before each experimental session, and all sessions will be scheduled after 10:00 am.

During the first experimental session, the participants will complete a battery of questionnaires, a baseline TD task, and a baseline food demand task (see the Primary Outcome Measures section below). Then, they will be randomly assigned to receive 1 of the 4 guided imagery intervention arms followed by manipulation check questions. Next, they will complete the TD and food demand tasks again, after which they will be offered a variety of snack foods to assess food choice. Food items will be placed next to the participants while a research assistant reads a standardized food choice script. At the end of the session, the participants’ anthropometric measurements will be taken, they will be scheduled for the second experimental session, and they will be instructed on when and how to complete the daily food diaries. The duration of the first session will be approximately 90 min, and each daily food diary entry will take approximately 5 min to complete. During the second experimental session, participants will complete the TD and food demand tasks again. They will be asked to complete another battery of questionnaires while they are again presented with a variety of snacks to eat, to assess their food choices a second time. The duration of the second session will be approximately 40 min. The schedule of enrollment, interventions, and assessments for the study is shown in Table 1.

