#### Food Choice

Food choice will be assessed by presenting participants with an array of healthy and unhealthy snack options after allocation and at closeout. Participants will be presented with the snack options on a tray, and all items will be presented as pairs (ie, 2 apples, 2 bags of chips, or 2 candy bars) to encourage selection. Participants will be presented with a total of 9 healthy and 9 unhealthy snack options (excluding drink options). Importantly, 2 of each snack option will be presented, so participants will see a total of 18 healthy and 18 unhealthy snack items (36 total snack items). Healthy snack food items have a total calorie count that ranges from 35 to 180 calories per portion. Unhealthy snack food items have a total calorie count that ranges from 230 to 330 calories per portion. An attempt was also made to match items categorically, for example, an unhealthy option such as potato chips will be provided along with a healthy option such as low-calorie popcorn and rice puffs. The snack items will be arranged neatly on the tray and will resemble the snack tray that is sometimes presented to guests in a hotel room. Alongside the tray, participants will be presented with accompanying unhealthy (soda) or healthy (water) drink choices. As with the snack, 2 of each drink option will be available.

Research assistants will describe the availability of the snack options in the context of the requirement that participants fast before the study appointment. This approach is expected to reduce potential participant bias that could occur if participants are aware their food choices will be recorded. The following is a section of the script that research assistants will deliver at this time:

In our lab, we always ask participants not to eat or drink anything before coming into the lab to make sure that differences in how hungry you are or the time since your last meal doesn’t affect your choices on the tasks or your preferences. We know it can be hard to fast and since we ask participants to not eat for two hours before coming in, we like to give people a range of snacks to eat.

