Participants will then be encouraged to select any snack option to eat during the session (while completing the final batch of questionnaires) or take the food(s) with them to eat later at their leisure. The research assistant will then leave the participant alone with the snack options while they complete the remaining questionnaire items. All food choices will be recorded by the research assistant after the participant departs. The recorded number of healthy and unhealthy snacks will be summed, respectively, to create *healthy food choice* and *unhealthy food choice* variables for each participant. These variables will be compared across treatment group as a between-subject variable and as a within-subject repeated measure variable, comparing the effect of the treatment (baseline compared with after allocation and at closeout).

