### Analysis

#### Primary Statistical Analysis

Our primary statistical analyses will comprise a mixed design (between-subjects and repeated measure) that compares TD, food demand, and food choice measures at baseline, after allocation, and at closeout across treatment arms. Our analyses will control for standard demographic variables such as age, biological sex, race, and income. A series of repeated measure ANOVAs with treatment arm as a between-subject variable and measurement period as the repeated measure will be conducted on TD rates and healthy and unhealthy food demand indices, respectively.

In addition, to examine the effect of the intervention arms on food choices inside and outside the lab, a series of ANOVAs will be conducted on healthy and unhealthy snack food choices and average daily serving intake values for each of the food categories. To probe the effect of the intervention on in-lab food choices, we will conduct a repeated measure ANOVA with measurement period repeated across treatment group on health and unhealthy snack food choices. Next, to probe the effect of the intervention on food choices outside the lab, we will conduct a 1-way ANOVA with treatment arm entered as the between-subject variable on average daily serving intake values for the primary food categories (ie, fruit and vegetable intake).

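### Food choice has no baseline measurement, yet the plan judges its treatment effect against baseline; the deciding term is unnamed and the 95% power does not carry over to this outcome

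*Protocol article*

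**What the plan says.** The Food Choice section fixes the measurement times: "Food choice will be assessed by presenting participants with an array of healthy and unhealthy snack options after allocation and at closeout". The Experimental Sessions section gives the same order for the first visit. Before allocation, participants complete "a baseline TD task, and a baseline food demand task". Randomization and the imagery recording follow, and the snack tray comes last: "Next, they will complete the TD and food demand tasks again, after which they will be offered a variety of snack foods to assess food" (…). Table 1 has baseline rows for TD and food demand and none for food choice.

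The analysis text reads differently. On the snack counts, the Food Choice section says "These variables will be compared across treatment group as a between-subject variable" and, in the same sentence, as a "within-subject repeated measure variable, comparing the effect of the treatment (baseline compared with after allocation and at closeout"). The Primary Statistical Analysis section opens with a mixed design that "compares TD, food demand, and food choice measures at baseline, after allocation, and at closeout across treatment arms". The abstract makes the same statement for the primary outcomes in general: "Analyses will compare primary outcome measures at baseline, postintervention, and at follow-up across treatment arms". For the in-lab snacks specifically, the plan is that "we will conduct a repeated measure ANOVA with measurement period repeated across treatment group on health and unhealthy snack food choices"; no term of that model is named as the test.

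The Sample Size section describes four arms and three periods (baseline, after allocation, closeout). It states 95% power at the .05 level for the arm-by-period interaction, with an effect size of 0.17 and 124 analysed.

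**The concern.** A comparison with baseline needs a baseline value, and for the snack task there is none. The daily diaries come after allocation. The food frequency questionnaire given before allocation is a different instrument and cannot stand in for a snack count.

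The contradiction affects interpretation. With a baseline among the periods, an arm-by-period interaction picks up a treatment effect, because the arms start level and then separate. Without one, the same term on two post-intervention occasions asks only whether the arms move apart or together between visit 1 and visit 2. An analyst who carried the powered term over to food choice would be testing persistence, whereas the predictions in the This Study section are differences between conditions in the choices made. The stated power would also be quoted for an outcome to which the calculation does not apply.

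**Working it through.** **Which outcomes have a baseline.** From Experimental Sessions, Table 1 and the outcome sections:

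| Outcome | Baseline | After allocation | Closeout |
|---|---|---|---|
| TD | yes | yes | yes |
| Food demand | yes | yes | yes |
| Food choice | no | yes | yes |

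The baseline contrast can be computed for the first two outcomes and not for the third.

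**Inputs for power.** From Sample Size: k=4 arms, m=3 periods, N=124 analysed, alpha 0.05, effect size 0.17. The metric is not named; I read it as Cohen's f. The document gives no within-person correlation rho, so I assume 0.5 and show 0.3 to 0.7. Sphericity and normal outcomes are also assumed.

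**Reproducing the plan's figure.** For the within-between interaction, lambda = f²·N·m/(1−rho), df1 = (k−1)(m−1), df2 = (N−k)(m−1).

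- lambda = 0.0289 × 124 × 3 / 0.5 = 21.50, df 6 and 240, power 95.1%. This matches the stated 95%, and 124 is the smallest multiple of four that reaches it.
- Dropout: 124/(1−0.20) = 155, or 156 for equal arms, as planned.

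**The same term on the two occasions that exist (m=2).**

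- lambda = 0.0289 × 124 × 2 / 0.5 = 14.33, df 3 and 120, power 89.3%.
- At rho=0.3 power is 75.7%; at rho=0.7 it is 98.9%.
- At rho=0.5, 95% power would need 156 analysed.

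**What that term detects.** If each arm's mean is shifted by the same amount at both visits, the visit 2 minus visit 1 difference has the same mean in every arm. The noncentrality is then 0, and the rejection rate equals alpha whatever the size of the shift. A simulation of 10,000 runs per scenario with 31 per arm, one arm shifted in most scenarios, gave:

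| Scenario, rho=0.5 | Interaction rejects | Arm main effect rejects |
|---|---|---|
| 0.5 SD at both visits | 5.1% | 62.0% |
| 0.8 SD at both visits | 4.9% | 97.3% |
| 0.5 SD at visit 1, gone by closeout | 49.3% | 18.6% |
| 0.8 SD at visit 1, gone by closeout | 90.8% | 42.5% |

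Over all sustained scenarios and rho 0.3 to 0.7, the interaction rejected in 4.6% to 5.2% of runs.

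**Power of the between-arm test if f=0.17 applied to it.** lambda = f²·N·m/(1+(m−1)·rho) = 0.0289 × 124 × 2 / 1.5 = 4.78.

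- Overall arm test, df 3 and 120: 41.0% (46.7% at rho=0.3, 36.5% at rho=0.7). At rho=0.5, 95% power would need 452 analysed.
- One factor of the 2×2 (EFT or PosA), df 1 and 120: 58% (64% at rho=0.3, 53% at rho=0.7).

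**The case against.** A reader might infer that the plan leaves only a test that cannot detect a lasting effect on food choice. The documents do not support that. The sentence containing the baseline contrast begins by planning a comparison across treatment groups as a between-subject variable. The repeated-measures ANOVA in the analysis section yields an arm main effect on two occasions, needs no baseline to be valid under randomization, and detects sustained differences in the table above. The paragraph on in-lab choices does not mention baseline and does not make the interaction decisive. It would therefore be an inference, not something the plan says, that a lasting shift would be reported as no effect.

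Two further points stand. An interaction produced by a fading effect is still caused by the intervention; it is an incomplete description of the effect, not a false one. And the baseline parenthesis repeats the wording used for food demand, where it is correct, so it may be carried-over text.

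None of this removes the contradiction. The contrast to which the Food Choice section attaches the effect of the treatment cannot be computed. The valid between-arm term is neither named as deciding nor given a power, and the only powered term relies on a period that this outcome lacks.

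**Conclusion.** The point holds as a contradiction about a primary outcome, visible from the text alone: a baseline comparison is planned for a measure with no baseline. This part rests on no assumption.

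The stated 95% power does not apply to food choice. On two occasions the interaction has about 89% power at f=0.17 (76% to 99% over the assumed correlations), and only the 5% error rate for an effect held equally at both visits. The zero noncentrality is exact; the power figures depend on the assumed rho, on reading 0.17 as Cohen's f, and on treating a count as normal.

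The 41% and 58% for between-arm tests are illustrations. They move an effect size predicted for the interaction onto a different term, and larger effects would have more power. They do not show that the trial is too small for food choice; they show that its power for that outcome is unstated and cannot be taken from the Sample Size section.

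**What to change.** - In Food Choice and in the opening sentence of Primary Statistical Analysis, delete the baseline comparison for food choice. In the abstract's Methods, limit the baseline statement to TD and food demand.
- Name the food-choice test: between-arm effects (EFT, PosA, EFT × PosA) on the healthy and the unhealthy counts over the two post-intervention visits. Keep arm-by-period as a description of persistence.
- In Sample Size, state that the 95% applies to TD and food demand only, and give separate power for the food-choice test with its assumed effect size and correlation.

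Adjusting for pre-allocation demand intensity is optional. That task covers one preferred healthy and one preferred unhealthy item, while the outcome sums over nine options of each kind, so it is only a proxy.

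The cost is wording, with no new data. Adding a snack task before the intervention would be a poorer remedy: it could reveal the concealed measure or affect later choices, and 84 participants had already completed the protocol at submission.

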#### Daily Food Diaries

To assess food choice during the 5 days between allocation and closeout, participants will be sent, by email, a link to complete a daily Web-based food diary. This questionnaire is based on the Paffenbarger Physical Activity Questionnaire Dietary Habits subscale [41] and other food frequency questionnaires. Participants will be asked to complete the survey at the end of the day when they do not plan on eating anything afterward. The survey will first ask the participants to briefly describe and/or list the food items or meals they ate that day. Then, participants will be asked to report the number of servings they ate that day for different food categories. The food categories will include fruits; vegetables; grains; eggs; milk and cream; dairy (not including milk); poultry; fish and seafood; beef, pork, lamb, and other red meat; nuts, seeds, and legumes; fats and oils; sweets and desserts (not including candy); candy; salty snacks; drinks; and other foods. For each food category, several examples will be provided to describe what equates to 1 serving of that category. The reported number of daily servings for each of the food categories will be averaged to create a measure of outside-the-lab food intake. For analysis, outside-the-lab food intake will be compared across treatment groups to assess the impact of the intervention arm on outside-the-lab food choices.

### Demographic and Anthropometric Measures

#### Demographic Information

Participants will self-report their age and biological sex (0=male, 1=female). They will also report their relationship status, education, and income group that best represents themselves from preselected options. Finally, they will be asked to report their racial and ethnic identity by indicating if they identify as Hispanic or Latino and select the racial group that best represents themselves from preselected options.

#### Anthropometric Measurements

During the first experimental session, height will be measured with a stadiometer and weight will be assessed with an electronic weight scale. Recorded height and weight will be used to confirm the participant’s self-reported height and weight on the screening questionnaire. Waist circumference will be measured with a tape measure. Body fat percentage will be assessed with an Omron bioimpedance scale. Blood pressure will be measured with an aneroid sphygmomanometer, Omron blood pressure monitor. Three successive arterial blood pressure readings will be taken on the participant’s left arm, with a 2-min interval between each reading.

### Covariates

Covariates thought to impact eating behavior will be assessed before allocation and 1 week later at closeout. Covariate measures are indicated in Table 1 in footnote f.

#### Perceived Stress

To control for the impact of stress on eating behaviors, we will measure self-reported perceived stress using the 14-item Perceived Stress Scale (PSS) [42]. The PSS assesses the extent to which situations in one’s life are appraised as stressful during the past month on a 5-point Likert scale (0=never, 4=very often).

#### Positive and Negative Affect

We will use the 10-item Positive and Negative Affect Scale (PANAS) [43] to control for the impact of dispositional affect on eating behaviors. The PANAS assesses the extent to which the individual felt positive or negative emotions in the past month. Participants rate their affect using a 5-point Likert scale ranging from very slightly or none at all to extremely. During the second experimental lab session, this questionnaire will be administered again, but instead ask about affect in the past week.

#### Depressive Symptoms

We will control for the impact of depression symptomatology on eating behavior by measuring depressive symptoms with the 10-item Center for Epidemiology Studies of Depression scale (CESD-10) [44]. The CESD-10 assesses mood symptoms during the past 7 days using a 4-point Likert scale.

#### Exploratory Measures

Several exploratory measures will be included in the study to determine if group assignment or our primary outcome measures are associated with psychological, behavioral, and emotional health constructs. Participants will complete a distinct set of exploratory assessments before allocation, after allocation, and at closeout (Table 1). Trait exploratory measures that are less likely to be impacted by the intervention content will be distributed after allocation and at closeout to also serve the practical design purpose of providing a consistent setting during which the participant is presented with the array of snacks that comprise the food choice measure. The description of each exploratory measure is provided in Multimedia Appendix 1.

### Analysis

#### Primary Statistical Analysis

Our primary statistical analyses will comprise a mixed design (between-subjects and repeated measure) that compares TD, food demand, and food choice measures at baseline, after allocation, and at closeout across treatment arms. Our analyses will control for standard demographic variables such as age, biological sex, race, and income. A series of repeated measure ANOVAs with treatment arm as a between-subject variable and measurement period as the repeated measure will be conducted on TD rates and healthy and unhealthy food demand indices, respectively.

In addition, to examine the effect of the intervention arms on food choices inside and outside the lab, a series of ANOVAs will be conducted on healthy and unhealthy snack food choices and average daily serving intake values for each of the food categories. To probe the effect of the intervention on in-lab food choices, we will conduct a repeated measure ANOVA with measurement period repeated across treatment group on health and unhealthy snack food choices. Next, to probe the effect of the intervention on food choices outside the lab, we will conduct a 1-way ANOVA with treatment arm entered as the between-subject variable on average daily serving intake values for the primary food categories (ie, fruit and vegetable intake).

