**Assessments**									
	Baseline: TD^b^	—	X	—	—	—	—	—	—
	Baseline: Food demand	—	X	—	—	—	—	—	—
	Outcome: TD	—	X	—	—	—	—	—	X
	Outcome: Food demand	—	X	—	—	—	—	—	X
	Outcome: Food choice	—	X	—	—	—	—	—	X
	Outcome: Daily food surveys	—		X	X	X	X	X	—
	Assessments before allocation^c^	—	X	—	—	—	—	—	—
	Assessments after allocation^d^	—	X	—	—	—	—	—	—
	Assessments at close out^e^	—		—	—	—	—	—	X
	Repeated assessments (before allocation and at close out)^f^	—	X	—	—	—	—	—	X

^a^—: not applicable.

^b^TD: temporal discounting.

^c^Assessments before allocation: food frequency, reward-based eating, health-specific self-efficacy, weight related eating, health locus of control, perceived stress reactivity.

^d^Assessments after allocation: emotion regulation, trait mindfulness, behavioral motivations, impulsiveness, mental health history, physical health history, demographics.

^e^Assessments at closeout: global self-reported health, self-reported weight status, social desirability, coping responses, tobacco and alcohol use, sleep quality, loneliness, psychological flexibility.

^f^Repeated assessments (before allocation and at closeout): stages of change in weight management; *Covariate measures included in analyses*: perceived stress, positive and negative affect, and depressive symptoms.”

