#### Food Demand

The food demand task will be given at baseline, after allocation, and at closeout. It is based on a food purchasing task [37] that assesses the amount participants are willing to pay (ie, reward value) for different quantities of snack foods. Participants will first view photos of different healthy (eg, apple, yogurt, and popcorn) and unhealthy (eg, potato chips, chocolate chip cookies, and candy bar) snack foods that correspond with the real food items they are presented with in the food choice task (see the Food Choice section below). Participants select their most preferred healthy food and their most preferred unhealthy food from the list and answer the questionnaire for each of the 2 food items. These preferred food photos are displayed on the computer during the task so that participants can refer to them when completing the task. The instructions, modified from the study by Epstein et al [40], are available in Multimedia Appendix 1.

Food demand task responses will be used to generate a food demand curve, reflecting the quantitative relationship between demand for food and escalating price. We will calculate the food demand curve for each of the preferred healthy and unhealthy options. Calculating the food demand curve generates 5 indices: (1) food demand breakpoint (ie, the first price at which consumption was 0), (2) intensity of food demand (ie, consumption at the lowest price), (3) elasticity of food demand (ie, sensitivity of snack food consumption to increases in cost), (4) Omax (ie, maximum expenditure for snack food), and (5) Pmax (ie, price at which expenditure was maximized). Calculating the food demand curve for each of the preferred or chosen healthy and unhealthy options will give rise to 10 values (5 indices for each healthy and unhealthy food categories). The primary index of demand will be intensity of food demand, which will be compared across treatment group as a between-subject variable and as a within-subject repeated measure variable, comparing the effect of the treatment (baseline compared with after allocation and at closeout). However, all indices will be calculated to fully describe the demand curve.

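### The food-choice models leave out pre-imagery snack demand, a related baseline already collected, while the text refers to a food-choice baseline that does not exist

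*Protocol article*

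**What the plan says.** Food choice is listed under Primary Outcome Measures. Its section gives two measurement times: "Food choice will be assessed by presenting participants with an array of healthy and unhealthy snack options after allocation and at closeout". Table 1 has baseline rows for temporal discounting and food demand, and none for food choice. Yet the Food Choice section ends by describing the analysis as "comparing the effect of the treatment (baseline compared with after allocation and at closeout", and the opening of Primary Statistical Analysis also lists food choice among the measures compared at baseline.

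Covariates appear in two places:

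- Primary Statistical Analysis: "Our analyses will control for standard demographic variables such as age, biological sex, race, and income".
- Table 1 footnote f, under a label saying that these covariate measures are included in the analyses: "perceived stress, positive and negative affect, and depressive symptoms". The Covariates section adds "Covariates thought to impact eating behavior will be assessed before allocation and 1 week later at closeout", and the subsections give the purpose, for example "To control for the impact of stress on eating behaviors, we will measure self-reported perceived stress" and "We will control for the impact of depression symptomatology on eating behavior by measuring depressive symptoms".

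Food demand is measured three times, first before the imagery (Experimental Sessions). Participants see photos of "snack foods that correspond with the real food items they are presented with in the food choice task", choose their preferred healthy and preferred unhealthy item, and answer the task for each. Intensity, meaning consumption at the lowest price, is the primary index. Nowhere is baseline demand named as a covariate for food choice.

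**The concern.** Temporal discounting and food demand each carry their own baseline into the repeated-measures model. Food choice cannot. How many snacks a person tends to take, whatever the arm, therefore stays in the between-person error unless another pre-randomisation variable explains part of it. The planned covariates describe demographics, stress and mood. None describes appetite for these kinds of snack, and the trial already holds a measure that does.

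Both tray presentations follow the imagery. A treatment effect that lasts over the five days therefore appears in the arm main effect, while the arm-by-period interaction asks only whether that effect changes between visits. The main effect is where between-person error matters. At stake is some precision on the only eating outcome observed directly, and some protection against chance differences in snack demand between arms of about 31. Separately, a text that promises a comparison with an uncollected baseline describes an analysis that cannot be run.

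**Working it through.** **Inputs from the protocol (Sample Size):** 156 recruited, 39 per arm; about 20% attrition; 124 analysed, 31 per arm; effect size 0.17; 95% power for the arm-by-period interaction at the .05 level; three measurement periods.

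**Assumptions, because the documents are silent:** 0.17 is Cohen's f; within-person correlation ρ = 0.5; sphericity. Let r be the joint partial correlation of the two baseline demand values with a participant's food choice averaged over both visits, beyond the planned covariates. No value of r is given, so a range is shown.

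**1. The plan's own figure.** For the interaction with g = 4 arms and m = 3 periods, λ = f²Nm/(1 − ρ) = 0.17² × 124 × 3 / 0.5 = 21.5, with (g − 1)(m − 1) = 6 and (N − g)(m − 1) = 240 degrees of freedom. Power is 95.1%, so the stated figure reproduces. For attrition, 124/0.8 = 155, against 156 planned. This calculation uses three periods; food choice has two.

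**2. Arm main effect on food choice, two periods, no demand covariate.** λ = f²Nm/[1 + (m − 1)ρ] = 0.17² × 124 × 2 / 1.5 = 4.78 on 3 and 120 degrees of freedom. Power is 41%, if f = 0.17 is carried over to this effect. That is an assumption; the protocol does not do so.

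**3. Effect of adding baseline demand.** Residual between-person variance is multiplied by (1 − r²), so:

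- λ from step 2 becomes λ/(1 − r²);
- the 124 analysed act like 124/(1 − r²);
- for one factorial main effect, 62 against 62, in outcome SD units, SE = (2/√124) × √(1 − r²) and power = Φ(0.5/SE − 1.96), with 0.5 SD assumed.

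| r | Variance cut | 124 act like | SE | Power, 0.5 SD main effect | Power, four-arm main effect, f = 0.17 |
|---|---|---|---|---|---|
| none | – | 124 | 0.180 | 79.5% | 41% |
| 0.1 | 1% | 125 | 0.179 | 79.9% | 41% |
| 0.2 | 4% | 129 | 0.176 | 81.1% | 43% |
| 0.3 | 9% | 136 | 0.171 | 83.1% | 45% |
| 0.4 | 16% | 148 | 0.165 | 85.9% | 48% |
| 0.5 | 25% | 165 | 0.156 | 89.5% | 53% |

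**4. Price of two coefficients.** The 0.5 SD column ignores the cost of estimating them. That cost inflates variance by roughly 2/118 = 1.7%, where 118 = 124 − 4 − 2. Break-even is near r = √0.017 = 0.13. At r = 0.1 there is effectively no gain, and a negligible loss.

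**5. Interaction.** A covariate that is constant over time cancels from within-person differences between visits. The arm-by-period test on food choice is not sharpened.

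**6. Chance imbalance.** The SE of a baseline difference in demand between two arms is √(2/31) = 0.25 SD. If r were 0.4, an imbalance of that size would shift the unadjusted contrast by 0.4 × 0.25 = 0.10 SD.

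**The case against.** The strongest reply is that nothing in the quoted sentence is wrong. Leaving out one prognostic covariate biases no randomised comparison, and a journal article need not print a full covariate list. Its demographic list is open-ended in any case. The first part stands: this is about efficiency. The second stands only in part. The article does name its covariates in two places and explains why each was chosen, and the measure nearest to the tray is in neither.

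A second reply is that demand may predict snack-taking poorly. Intensity is a questionnaire answer about one healthy and one unhealthy item. The outcome counts items over 9 healthy and 9 unhealthy options, two of each, eaten or taken away. Someone keen on one item may take a single snack. This stands, and it is why r is shown down to 0.1.

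A reader might infer from the analysis section alone that the models adjust only for demographics. Table 1 footnote f and the Covariates section rule that out, so r has to be read as what demand adds beyond stress, affect and depressive symptoms as well. A reader might also infer that every comparison on food choice loses precision. It does not: the arm-by-period interaction, the effect used in the sample size calculation, is untouched.

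**Conclusion.** The point holds as a modest, nearly free improvement. Food choice has no baseline; a related pre-randomisation measure is already collected; the named covariates omit it; and two passages refer to a food-choice baseline that Table 1 and the Food Choice section show is not taken.

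The gain falls on the arm and factorial main effects. It runs from nothing useful at r = 0.1 to a 25% cut in residual between-person variance at r = 0.5, which takes power for an assumed 0.5 SD main effect from 79.5% to 89.5%. These figures depend on an unknown partial correlation and on the assumed effect sizes.

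The documents do not support calling this a bias or a fault in the sample size: the 95% figure reproduces for the effect it was calculated for. Nor do they support calling baseline demand a close stand-in for snack counts.

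**What to change.** 1. In the food-choice models, for healthy and for unhealthy counts, prespecify pre-imagery healthy and unhealthy demand intensity as covariates alongside those already planned. Fix one scale in advance, for example log(x + 1), rather than choosing it after seeing the data. Use the baseline values only; the later demand values may be affected by the intervention.
2. In the Food Choice section and the opening of Primary Statistical Analysis, remove the statement that food choice is compared with baseline. State that it is compared across arms after allocation and at closeout.

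Cost: two degrees of freedom out of 120, a line of analysis text and a wording correction. No new data are needed and nothing changes for participants.
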